**Primary outcomes**							
	Self-reported stress	Patients and caregivers	VAS^a,stress^	Yes	Yes	Yes	Yes
	Self-reported pain	Patients	VAS^pain^	Yes	Yes	Yes	Yes
	Anxiety and depression	Patients	HADS^b^	Yes	Yes	Yes	Yes

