### Outcome Variables

#### Research Question 1 (Primary and Secondary Outcome Variables)

Stress, anxiety, and pain represent the primary outcome variables that will be measured using paper-and-pencil questionnaires.

The secondary outcome variables were overall quality of life, emotional status, mental well-being, self-efficacy perception, and patient activation during and after hospital stay.

To assess the primary outcome variables, the following questionnaires will be used after each standard care visit and will be administered by paper and pencil:

Patients’ and caregivers’ *self-reported stress* was measured using a VAS at enrollment (baseline), at admission for surgery, at hospital discharge, and 2 weeks after surgery. Operationally, a VAS is usually a horizontal line, 100 mm in length, anchored by word descriptors at each end, such as no stress versus highest stress possible [37].Patients’ *self-reported pain* was measured using a VAS for pain measurement at enrollment (baseline), at admission for surgery, at hospital discharge, and 2 weeks after the surgery. The VAS for pain is a validated single-item scale that is anchored by “no pain” (score of 0) and “pain as bad as it could be” or “worst imaginable pain” (score of 100). The VAS presents a high internal consistency, as shown by a Cronbach α of 0.9117 [38].Patients’*Hospital Anxiety and Depression Scale* (HADS) scores were measured at admission for surgery, at hospital discharge, and 2 weeks after surgery. The HADS consists of 2 dimensions with 7 questions each, one representing the anxiety subscale and the other representing depression, with both psychopathological concepts of anxiety and depression being independent. Each item was rated on a 4-point frequency scale, ranging from 0 to 3. The internal consistency of the HADS, as measured by the Cronbach α coefficient, was found to be .78 for the anxiety subscale and .86 for the depression subscale, indicating satisfactory reliability [39].

To assess the secondary outcome variables, the following questionnaires will be used after each standard care visit and will be administered paper and pencil:

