### Sample Size

As this was a feasibility study, a sample size calculation is not required. However, we can estimate the number of participants we will be able to recruit during the data-collection period. In this feasibility study with a statistical power of 0.8, an α of .05, and an effect size of 1.20, the minimum required sample size will be 60 participants (30 in each group). Sample size calculations are estimated using G*Power (version 3.1.9.2).

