#### Randomization and Allocation

Participants-patients will be randomized through the prestratified randomization method to achieve balance between the 2 groups (intervention and control groups) according to the type of surgery and baseline characteristics (covariates). Stratified randomization was achieved by generating a separate block for each combination of covariates and participants were assigned to the appropriate block of covariates. The specific covariates in the clinical trial were represented by the type of surgery (3 surgeries) and sex (2 levels: male and female). With these 2 covariates, the possible block combinations totaled 6 (eg, male, cardiac valve replacement). According to this, the participants’ allocation will be blinded through an Excel file spreadsheet (RAND function) using permuted block randomization with a ratio of 1:1 between the intervention and control groups. Allocation concealment will be ensured, as we will not release the randomization code until the patients are recruited for the trial.

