### Data Analyses

The analyses will be conducted in Python 3.9.5 through the IDE PyCharm Community Edition 2021.2.1 Software and intention-to-treat principles. Descriptive statistics will be used to characterize the groups during the 4 visits. Furthermore, owing to the small sample size, Spearman correlations will be performed with all the variables to check, first, for potential associations between the variables and, second, differences between the intervention versus control groups. Further potential differences between these groups will be analyzed as follows:

Stress (VAS), pain (VAS), and mood state (PANAS-short form) will be subjected to a multivariate mixed analysis of variance (split-plot ANOVA) with “time” as a within-subject factor (ie, 4 time points) and “group” as a between-subject factor (intervention vs control).Patient activation (PAM-13) and self-efficacy (GSE-SF) will also be submitted to a multivariate mixed analysis of variance with “time” as a within-subject factor (Ie, 3 time points) and “group” as a between-subject factor (intervention vs control).Mental well-being (Short Warwick Edinburgh Mental Well-Being Scale) and HRQoL (EQ-5D-3L and EQ-5D-Y) will be analyzed using multivariate mixed analyses of covariance. As measurements of these 2 variables are based on a pre-post design, postmeasurements will be used as the dependent variable and premeasurements as covariates.

Finally, it is of interest to explore the effects as a function of different types of surgery. To this end, 2 different statistical approaches will be used:

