Cluster analyses per surgery type. Data will be split for each of the surgeries, and variables will be analyzed individually using time and group as within and between factors, respectively.A different statistical approach from the approach described above will also be used. In this case, analyses are performed within a linear mixed model (LMM) framework. LMM allows for the flexible handling of unbalanced data, outliers, or missing observations without averaging the data of participants. In addition, LMM enables the modeling of data using different fixed and random factors. Accordingly, each of the variables will be submitted to an LMM analysis wherein “time,” “group (intervention vs control)” and their interaction (time × group) will be included as fixed factors. In contrast, “subjects” and “surgery” will be submitted as random factors. This analysis enables the calculation of regression estimation parameters by considering that participants differ in the surgery type. In addition, the participants’ age or sex may also be used as control covariates.

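### Stress, pain and PANAS are analysed with the baseline score as one of four time levels, not as a covariate, so their analysis is valid but less precise than the one planned for well-being and EQ-5D

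*Protocol article*

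**What the plan says.** Table 1 lists stress and pain (VAS) as primary outcomes, each measured at all four visits. The outcome section gives the times for stress as "at enrollment (baseline), at admission for surgery, at hospital discharge, and 2 weeks after surgery"; pain and PANAS follow the same schedule. The Data Analyses section puts these three into a split-plot ANOVA with time "as a within-subject factor (ie, 4 time points) and" group between subjects, so the baseline score is one of the four outcome levels. The section does not say whether the group main effect or the interaction answers the question, and it names no contrast.

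For mental well-being and health-related quality of life, both secondary, the same section takes another route: "postmeasurements will be used as the dependent variable and premeasurements as covariates". The reason given is that these two have a pre-post design. In Table 1, however, EQ-5D-3L has three measurements (baseline, admission, discharge).

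A linear mixed model is then added for each variable, under the aim of exploring effects by type of surgery. It has time, group "and their interaction (time × group) will be included as fixed factors", with subject and surgery as random factors. Age or sex are the only optional covariates named. The text says that this model gives regression estimates.

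**The concern.** The first research question asks how far the program changes stress, anxiety and pain, which calls for an estimate of an effect after baseline. A group main effect over four visits mixes three follow-up visits with one at which little or no effect is expected, so it understates a sustained effect. The interaction test uses 3 df and says only that the two profiles differ somewhere. Neither uses the baseline score to remove between-patient variation, although the score is collected and the plan uses this device for two secondary outcomes. At stake is precision in a trial of 60 patients, and clarity about which number is the treatment effect.

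**Working it through.** **The plan's own figure.** The Sample Size section works "with a statistical power of 0.8, an α of .05, and an effect size of 1.20" and arrives at 30 per group. A two-sided two-sample t test at those inputs needs 11.94, so 12 per arm. With 30 per arm, power at 1.20 is 0.995, and 80% power is reached at 0.74 SD. The stated size therefore does not follow from 1.20. That is a separate matter, but it is why a smaller effect is also examined here.

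**Inputs from the protocol.** n = 30 per arm, 1:1 allocation, four visits with baseline first, two-sided alpha 0.05 (the sidedness is my assumption).

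**Assumptions not in the protocol.** Equal SDs (set to 1), the same correlation ρ between any two visits (0.3, 0.5, 0.7), no dropout, no expected baseline difference, and an effect d = 0.5 SD that is the same at all three follow-up visits. Power comes from the noncentral F distribution with noncentrality λ.

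**Formulas, with ρ = 0.5 put in (n/2 = 15, d² = 0.25).**

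1. Group main effect. Expected difference (0 + d + d + d)/4 = 0.75d = 0.375. Variance of a four-visit mean (1 + 3ρ)/4 = 0.625. λ = 15 × 0.375²/0.625 = 3.375 on 1 and 58 df.
2. Time-by-group interaction. Squared deviations from the profile mean: (0.75d)² + 3(0.25d)² = 0.75d² = 0.1875. λ = 15 × 0.1875/(1 − ρ) = 5.625 on 3 and 174 df.
3. Change-from-baseline contrast available from the mixed model (mean of follow-up visits minus baseline). Variance (1 + 2ρ)/3 + 1 − 2ρ = 0.667. λ = 15 × 0.25/0.667 = 5.625 on 1 df, with 58 to 174 denominator df.
4. Mean of follow-up visits adjusted for baseline. Residual variance (1 + 2ρ)/3 − ρ² = 0.417. λ = 15 × 0.25/0.417 = 9.0 on 1 and 57 df.

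| Power, d = 0.5 sustained | ρ = 0.3 | ρ = 0.5 | ρ = 0.7 |
|---|---|---|---|
| 1. Group main effect | 0.545 | 0.439 | 0.368 |
| 2. Interaction, 3 df | 0.353 | 0.480 | 0.720 |
| 3. Change contrast (58 to 174 df) | 0.505–0.513 | 0.645–0.655 | 0.853–0.861 |
| 4. Baseline-adjusted mean | 0.816 | 0.839 | 0.928 |

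Lines 2 and 3 have the same λ. For a sustained effect, the gap between them is the price of spreading one contrast over 3 df, and the gap between lines 3 and 4 is the price of not adjusting. In variance terms, line 3 against line 4 is 0.933/0.443 = 2.1, 0.667/0.417 = 1.6 and 0.400/0.310 = 1.3 at ρ = 0.3, 0.5 and 0.7.

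**Same check at d = 1.20, sustained.** Main effect 0.999/0.991/0.973, interaction 0.987/0.999/1.000, and lines 3 and 4 at 0.997 or more throughout.

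**Effect at one visit only, d = 0.5** (ρ = 0.3/0.5/0.7). Interaction 0.353/0.480/0.720. Baseline-adjusted contrast at that visit, if named beforehand, 0.514/0.594/0.760. Baseline-adjusted average over visits 0.159/0.166/0.207.

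**The case against.** A reader might infer that the plan offers no effect estimate at all, only a diluted main effect or an omnibus p-value. The protocol does not support that. With baseline as the reference level, the mixed model's time-by-group coefficients are between-group differences in change from baseline at admission, discharge and day 14. They are undiluted estimates, and line 3 above is the fair comparator for them. What remains is that this model is introduced for surgery type, names no target contrast and does not adjust for baseline.

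A reader might also infer that the analysis is biased or the tests invalid. They are not: a split-plot ANOVA with baseline as a level gives a valid interaction test. Nor is the interaction always the weaker choice. For an effect at one visit only, it beats the baseline-adjusted average, and the adjusted single-visit contrast wins only if the right visit was named in advance.

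Nor can one say flatly that no effect is possible at baseline. The intervention group receives the solution and training during the first visit, and questionnaires are given following each visit, so the order of baseline scoring, allocation and exposure is left open. If scoring comes last, both the 0.75 factor and the covariate remedy weaken.

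Finally, the correlation, the effect profile and d = 0.5 are not the protocol's figures, and at its own 1.20 a sustained effect would be found by any of these methods. That stands as a limit on the power argument. It does not change the 0.75 factor, which needs no correlation and holds for any sustained d when baseline precedes exposure.

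**Conclusion.** The point holds as one of precision and clarity. Baseline is an outcome level for two primary outcomes (stress and pain) and for PANAS, so the four-visit group main effect shows 75% of a sustained effect if baseline precedes exposure. Under the stated assumptions, the best contrast the plan already supplies has power of about 0.51/0.65/0.85, against 0.82/0.84/0.93 with baseline adjustment. The gain is thus large at low correlation and modest at 0.7. The pre-post reason for treating well-being and EQ-5D differently does not explain the split, since EQ-5D also has three measurements. This is a worthwhile improvement, not the correction of an invalid analysis.

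**What to change.** In Data Analyses, for stress and pain, and likewise for PANAS:

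- Model the admission, discharge and day-14 scores as outcomes, with the baseline score and its interaction with visit as covariates. Do the same for HADS anxiety where a baseline score exists: Table 1 schedules one, but the outcome text lists HADS only from admission onward.
- Name in advance whether one visit (and which) or the average over visits is the main contrast.
- Report adjusted mean differences with 95% confidence intervals at each visit and averaged over visits.
- Do not read the four-visit group main effect as the treatment effect.
- State whether baseline questionnaires were completed before allocation and before the solution was handed over. The covariate approach applies where they were.

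The cost is analysis wording only. Baseline VAS and PANAS scores are already scheduled, and no new data are needed. The Results section says that recruitment is complete and analysis is ongoing, so the change should be documented before comparative results are seen, or else labelled post hoc.

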### Interventions

#### Overview

Eligible participants will be randomly assigned to the experimental group or the control group following block randomization of size 4 using the Sealed Envelope web-based tool [36]. The digital health solution includes 3 distinct components—that is, the mobile app, a VR component, and a clinical web application. The first and second components will be used by the participants in the experimental group, whereas the third will be used only by HCPs for those patients. Both the control and the experimental groups underwent the same visits. The trial was organized as shown in Figure 5.

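### Randomisation is stratified by surgery type and sex, but the ANOVAs and ANCOVAs omit both and the mixed model makes sex optional, so the group comparison is conservative to the extent that the strata predict outcome

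*Protocol article*

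**What the plan says.** Randomization and Allocation names the stratification factors: "The specific covariates in the clinical trial were represented by the type of surgery (3 surgeries) and sex (2 levels: male and female". That makes six strata, filled by "permuted block randomization with a ratio of 1:1 between the intervention and control groups". The Overview under Interventions gives a block size of 4.

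Data Analyses then states the factors of each model:

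- **ANOVAs.** "Stress (VAS), pain (VAS), and mood state (PANAS-short form) will be subjected to a multivariate mixed analysis of variance (split-plot ANOVA", with time within patients and group between patients. Patient activation and self-efficacy have the same structure. Neither surgery type nor sex appears.
- **ANCOVAs.** For mental well-being and quality of life, the post score is the outcome and the pre score is the only covariate named.
- **Linear mixed model.** Time, group and their interaction are fixed; subjects and surgery are random. The text adds that a participant's "age or sex may also be used as control covariates".
- **By surgery.** A further analysis splits the data by surgery and repeats the time and group analysis within each part.

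The Confounding Variables section says firmly that age, sex and surgery type will be used in that role. It does not say in which model, and it places them in one list with length of stay, complications, reoperation and mortality.

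**The concern.** When allocation is balanced within strata, differences between strata cannot contribute to the difference between arms. A model that leaves the strata out still counts those differences as error. Its standard error is then larger than the true sampling variation, its test rejects less often than the nominal 5% under the null, and part of the gain from stratifying is lost. In a trial of 60 patients that covers cardiac, urological, orthopaedic and paediatric surgery, the strata could well predict pain or stress.

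The article also gives three different answers on adjustment: a firm commitment in Confounding Variables, silence in the ANOVAs and ANCOVAs, and an option for sex in the mixed model. An analyst following Data Analyses as written would leave both factors out of the ANOVAs for stress and pain, which are primary outcomes.

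**Working it through.** **Inputs from the article.** 30 patients per arm, 1:1, six strata, blocks of 4; two-sided 5% level (sidedness is not stated, so this is assumed).

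**Inputs assumed.** R2, the share of between-patient outcome variance explained by surgery type and sex. The article does not give it, so a range is shown. Outcome SD is set to 1.

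**1. The article's own figure.** Sample Size states a calculation "with a statistical power of 0.8, an α of .05, and an effect size of 1.20" and concludes that "the minimum required sample size will be 60 participants (30 in each group". A two-sample t-test with d = 1.20, 80% power and two-sided 5% needs 12 per arm, so the stated 30 is not reproduced. That is a separate matter. For this point, 30 per arm gives 99.5% power at d = 1.20 and 80% power at d = 0.736.

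**2. Group effect, unadjusted.**

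- Reported SE = sqrt(2/30) = 0.258.
- True SE under stratified allocation = sqrt((1 − R2) × 2/30).
- Ratio = 1/sqrt(1 − R2).
- Type I error ≈ 2 × [1 − Φ(2.002/sqrt(1 − R2))], where 2.002 is the t critical value on 58 degrees of freedom.

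| R2 | True SE | Reported/true | Type I error | Power at d = 0.736, unadjusted | Adjusted |
|---|---|---|---|---|---|
| 0 | 0.258 | 1.000 | 4.5% | 80.2% | 80.0% |
| 0.1 | 0.245 | 1.054 | 3.5% | 81.5% | 83.9% |
| 0.2 | 0.231 | 1.118 | 2.5% | 82.9% | 87.9% |
| 0.3 | 0.216 | 1.195 | 1.7% | 84.5% | 91.7% |
| 0.4 | 0.200 | 1.291 | 1.0% | 86.3% | 95.1% |

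The 4.5% in the first row arises because the formula pairs a t critical value with the normal distribution. Simulation gives 4.9% there.

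**3. Fixed or random surgery.** Simulation: 2,500 trials per setting, 60 patients, blocks of 4 within six strata, one value per patient, surgery explaining 20% and sex 5% of variance.

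| Model | Mean SE | Power at d = 0.736 |
|---|---|---|
| No strata | 0.258 | 83.6% |
| Surgery random, no sex | 0.231 | 88.4% |
| Surgery random, plus sex | 0.223 | 90.3% |
| Surgery and sex fixed | 0.224 | 90.2% |

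Type I error without strata was 2.5% in this setting.

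**4. ANCOVA.** Assume the strata explain 20% of variance, their effect is constant over time, and the within-stratum pre–post correlation is 0.5.

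- Within-stratum variance is 0.8 and within-stratum covariance 0.5 × 0.8 = 0.4. The overall covariance, and so the slope, is 0.2 + 0.4 = 0.6.
- Reported residual variance = 1 − 0.6² = 0.64.
- True variance = 0.8 + 0.6² × 0.8 − 2 × 0.6 × 0.4 = 0.608.
- SE ratio = sqrt(0.64/0.608) = 1.026, which is about 3% too wide.

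**5. Time by group.** This test uses contrasts within patients. A surgery or sex effect that is the same at every visit cancels, so it costs nothing. A loss needs courses that differ by surgery, and a random intercept for surgery does not absorb those. As an illustration with assumed pain means (mm, four visits) of 10, 10, 40, 25; 55, 55, 45, 35; and 15, 15, 35, 20 in three surgery groups, SD 20, correlation 0.5, and a 10 mm postoperative effect, two simulations of 5,000 trials each gave:

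| Differences between courses | Type I error without surgery × time | Power without | Power with |
|---|---|---|---|
| As assumed | 0.8% to 1.1% | 35% | 60% to 62% |
| Halved | 3.4% to 3.5% | 55% | 62% |
| Quartered (one simulation) | 4.5% | 60% | 62% |

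**6. Power at the article's effect size.** At d = 1.20 the unadjusted test already has at least 99.5% power, so adjustment can add at most 0.5 percentage points.

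**The case against.** The article does commit, in Confounding Variables, to using sex and surgery type, so it could be said that adjustment is planned and only its placement is missing. This stands in part. The section names no model, and the models that are set out do not contain the terms. The passages have to be reconciled, and the commitment alone does not repair Data Analyses.

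The error is also conservative: it produces no excess of false positives, it vanishes if the strata do not predict outcome, and this is a feasibility study. All of that is true. It limits the weight of the point but does not remove it, because the first research question asks how far the program affects stress, anxiety and pain, and interval width bears on that answer.

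The separate analyses by surgery do remove surgery level and course from the error term. They are exploratory, however, and do not change the pooled tests.

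A reader might infer four stronger things that the documents do not support:

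- **That treating surgery as random is itself the fault.** For the group effect it recovers most of the gain, and all of it once sex is added (0.223 against 0.224). A variance estimated from three levels is imprecise, but that is a lesser objection.
- **That every interval and p-value is wrong by the amounts in the first table.** Those figures apply to the unadjusted group effect only.
- **That a large loss in the time by group test has been shown.** It rests on assumed pain courses and shrinks quickly as they converge. Nothing was computed for stress or anxiety.
- **That covariates will be picked after seeing the data.** The Results section says only that recruitment is complete and analysis is under way. An analysis plan not shown here may already fix the choice.

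**Conclusion.** The point holds in a conditional form. The stated ANOVAs and ANCOVAs leave out both randomisation factors, the mixed model makes one of them optional, and the Confounding Variables section says otherwise.

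The consequence is lost precision, not bias. For the unadjusted group effect it amounts to about 5%, 12% and 20% on the standard error at assumed R2 of 0.1, 0.2 and 0.3, and at d = 0.736 to roughly 2, 5 and 7 points of power. In the ANCOVAs it is much smaller. In the time by group test it depends entirely on whether courses differ by surgery. That is plausible for pain, since some patients awaiting joint replacement can be expected to have pain beforehand while others have it mainly afterwards, but the documents give no values. At the article's own effect size the power loss is negligible.

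**What to change.** - Include surgery type, coded as randomised, and sex in every between-arm ANOVA, ANCOVA and mixed model. State the coding: Randomization and Allocation counts three surgeries, while the inclusion criteria list eight entries.
- Add surgery type by visit wherever time by group is the test of interest.
- Replace the optional wording for sex in the mixed model with a firm inclusion, and state now whether age is included.
- Reconcile this with Confounding Variables. Adjust the arm comparison only for variables fixed before randomisation. Length of stay, complications, reoperation and mortality arise afterwards and should not be covariates in it.

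Surgery may stay as a random factor for the group effect; deleting it is not required.

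The cost is wording and a few degrees of freedom. With three surgery groups, surgery (2) and sex (1) take the between-patient residual from 58 to 55. Surgery by visit over four visits takes 2 × 3 = 6 from the 58 × 3 = 174 within-patient degrees of freedom. No new data are needed, because both factors were used to randomise.
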